#### Interim analyses

Data will be performed at any interim analysis only by blinded data analysts, and the trial steering committee will have access to these interim results and make the final decision to terminate the trial.

#### Methods for additional analyses (e.g., subgroup analyses)

Subgroup analyses are not planned for this study.

#### Methods in analysis to handle protocol non-adherence and any statistical methods to handle missing data

The primary analysis will follow an intention-to-treat (ITT) approach, including all participants as randomized, regardless of protocol adherence.

Missing data will be addressed using multiple imputation methods, assuming data are missing at random. Imputation models will include baseline characteristics, group assignment, and observed outcome values.

Sensitivity analyses will be conducted to assess the robustness of the results under different missing data assumptions, including complete case analysis and worst-case scenario imputation.

#### Plans to give access to the full protocol, participant level-data and statistical code

The datasets of this study are available on the clinical trial registration website.

### Oversight and monitoring

#### Composition of the coordinating center and trial steering committee

A Trial Steering Committee (TSC) will be established to ensure quality assurance, oversee protocol amendments, monitor the conduct of the study, and assess outcomes. The TSC will meet regularly to closely supervise trial progress. It will have unblinded access to study data and will determine whether to continue the trial based on assessments of safety, efficacy, and compliance.

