### Statistical methods

#### Statistical methods for primary and secondary outcomes

The primary outcome of this study is the change in MoCA scores from baseline to post-intervention and follow-up. The changes in MoCA scores from baseline to post-tDCS intervention, and during the follow-up assessment, will be compared between the experimental and control groups. Homogeneity of variance will be assessed by Levene’s test. For normally distributed continuous data, ANOVA will be used to compare differences between the two groups. If ANOVA indicates significant differences, further post-hoc analysis will be performed using Bonferroni correction. For non-normally distributed continuous data, the Wilcoxon test will be used. The significance level (α) for statistical hypothesis testing will be set at *P* < 0.05. Differences with *P* < 0.05 will be considered statistically significant, while those with *P* > 0.05 will be considered not statistically significant.

Secondary outcomes, including changes in DST, TMT-A and TMT-B, and MBI scores, will be analyzed using similar repeated measures ANOVA methods. For non-normally distributed continuous data, the Wilcoxon signed-rank test will be used for within-group comparisons, and the Mann-Whitney U test will be used for between-group comparisons. fNIRS data will be analyzed using mixed-effects models to assess changes in cortical activation and connectivity, accounting for random effects of participants and fixed effects of group and time. Correlation analysis, such as Pearson correlation coefficient or Spearman correlation coefficient will be conducted to explore the relationships between primary and secondary outcome measures. Lesion location (cortical/subcortical), stroke subtype (ischemic/hemorrhagic), hemispheric lateralization (left/right) and stroke phase (subacute/chronic) will be recorded based on imaging reports. Exploratory analyses may include lesion location and laterality as covariates if appropriate, to explore their influence on intervention outcomes.

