#### Composition of the data monitoring committee, its role and reporting structure

Neurologists, methodologists, and statisticians will supplement the data monitoring committee (DMC). The DMC will be responsible for overseeing data quality management and safety monitoring. DMC meetings will be held regularly. Clinical Trial Data Management issued by the Chinese National Medical Products Administration.

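### The steering committee that oversees amendments and conduct also has unblinded data and decides continuation partly on efficacy, which the fixed-sample size and single 0.05 level do not allow for

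*Protocol article*

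**What the plan says.** Four parts of the protocol article bear on this.

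- **Composition of the coordinating center and trial steering committee.** The TSC's tasks include to "oversee protocol amendments, monitor the conduct of the study, and assess outcomes". On its meetings: "The TSC will meet regularly to closely supervise trial progress". On its access and powers: "It will have unblinded access to study data and will determine whether to continue the trial based on assessments of safety, efficacy, and compliance".
- **Interim analyses.** The wording is "Data will be performed at any interim analysis only by blinded data analysts", and it continues that "the trial steering committee will have access to these interim results and make the final decision to terminate the trial". No number or timing of looks is given.
- **Composition of the data monitoring committee.** Neurologists, methodologists and statisticians are named, but the remit is narrow: "The DMC will be responsible for overseeing data quality management and safety monitoring". The section does not say that the DMC is independent of trial conduct.
- **Statistical methods and Sample size.** One level is given for all testing: "The significance level (α) for statistical hypothesis testing will be set at *P* < 0.05". The sample size section plans one two-sided comparison at 0.05 with 90% power, giving 24 evaluable and 30 enrolled per group.

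The trial design and blinding sections blind participants, outcome assessors and the data analyst. They do not mention the TSC.

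**The concern.** Two separate problems follow from what the text states.

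**Bias in decisions.** A committee that knows the results by arm should not also oversee changes to the trial. If an amendment follows an unblinded review, nobody can later show that the results did not prompt it. This holds however many looks take place, and a stopping boundary would not cure it, because the problem is who sees what.

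**Type I error.** Efficacy is named as a ground for continuing or not, and the committee that decides holds the comparative data. The stated sample size and significance level suit one test at the end. If the trial were stopped on a favourable unadjusted result, the chance of a false positive would exceed 5%, and the effect estimate at an early stop would tend to be too large.

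The body better placed to hold unblinded data, the DMC, has no role in either decision beyond safety.

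**Working it through.** **1. The plan's own sample size.** Inputs from the Sample size section: means 25.7 and 23.7 (difference 2.0), SDs 2.4 and 1.7, two-sided alpha 0.05, power 0.90, dropout 20%.

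- Stated formula: n = (1.96 + 1.28)² × (2.4² + 1.7²) / 2.0² = 10.4976 × 8.65 / 4 = 22.70, so 23 per group.
- Welch t-test with the noncentral t distribution: power 0.889 at 23 per group and 0.902 at 24. This gives 24, as the article reports.
- Dropout: 24 / (1 − 0.20) = 30 per group, 60 in total.

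The figure reproduces. It is a fixed-sample number with no allowance for interim testing.

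**2. Who holds what.**

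| Function | Body named in the article |
|---|---|
| Overseeing amendments, monitoring conduct, assessing outcomes | TSC |
| Unblinded access to study data | TSC |
| Receiving interim results, final decision to terminate | TSC |
| Continuation on safety, efficacy and compliance | TSC |
| Data quality and safety monitoring | DMC |

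The first four functions sit in one committee. The bias point follows from this table alone and needs no arithmetic.

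**3. Conditional size of the type I error problem.** The article fixes no looks, so these are assumptions: K equally spaced analyses including the final one, a two-sided test at |Z| > 1.96 at each, and a stop with a claim of success whenever the limit is crossed. With information fractions t = k/K and Z_k = B(t)/√t, where B is Brownian motion without drift, the overall error is P(|Z_k| > 1.96 for at least one k).

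| Interim looks | Analyses K | Overall type I error (numerical integration) | Simulation, Welch t, 24 per group, 100,000 runs |
|---|---|---|---|
| 0 | 1 | 0.050 | 0.051 |
| 1 | 2 | 0.083 | 0.085 |
| 2 | 3 | 0.107 | 0.109 |
| 3 | 4 | 0.126 | 0.128 |
| 4 | 5 | 0.142 | not run |

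If the review of efficacy could lead only to stopping for futility, the overall error would not exceed 0.05.

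**4. A boundary that would hold 5%.** For one look at 50% information, the Lan-DeMets O'Brien-Fleming-type function spends 4 × [1 − Φ(2.2414/√0.5)] = 0.00305 at the interim (|Z| > 2.963). Solving for the final limit gives |Z| > 1.969, nominal P = 0.0490. The classical O'Brien-Fleming boundary gives 0.0052 and 0.0480. These are two variants that both hold 5%, so the plan must name the one it uses.

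**The case against.** **A boundary may exist elsewhere.** Looks, boundaries and alpha spending often sit in an analysis plan or committee charter, and neither is shown. A reader might infer that no boundary exists and that type I error is uncontrolled. The documents do not support that; they show only that none is stated here. What stands is what the article does state: efficacy-based continuation by an unblinded committee, beside a fixed-sample size and a single 0.05 level.

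**The illustration may not describe this trial.** This is correct. The interim sentence is garbled and may mean only that blinded analysts do any interim analysis that occurs. Regular TSC meetings are described as supervision, and the 0.05 level is not expressly applied to interim looks. Efficacy review could also mean futility only, although the text does not limit it to that. So 8.3% to 14.2% is not this trial's error rate.

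**The TSC's powers can be overstated.** A reader might infer that it runs the trial, or can change endpoints or eligibility by itself. The text says that it oversees amendments and monitors conduct. The auditing section has a dedicated individual conduct and monitor the trial, and revised protocols go to the IRB for approval. That approval does not remove the risk that an amendment is prompted by known results.

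**Blinded analysts and an unblinded TSC can coexist.** A reader might see a contradiction. If analysts work with coded groups and the committee holds the code, there is none. It is an ambiguity to clear up. Participants and outcome assessors stay blinded, so nothing here shows that MoCA measurement is compromised.

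**The trial is called exploratory.** This lowers the stakes, but the article still has a superiority hypothesis, 90% power and a significance rule at 0.05.

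**Conclusion.** The concern holds in a limited form. The article places amendment oversight, conduct monitoring, unblinded data and an efficacy-based decision to continue in one committee, and restricts the DMC to data quality and safety. The exposure of later decisions to results by arm follows directly from the text. The type I error part is conditional: the text permits efficacy stopping that the 24 evaluable per group and the single 0.05 level do not provide for. Under the assumed 1 to 4 equally spaced looks at unadjusted 0.05, the error would be about 8.3% to 14.2% against the stated 5%. It would stay at or below 5% with futility-only stopping or with a valid boundary held in a document not shown. Given that uncertainty and the exploratory label, this should be fixed but does not by itself invalidate the design.

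**What to change.** Rewrite the interim analyses and steering committee sections to say that:

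- no interim analysis will be done for efficacy stopping;
- the TSC stays blinded to outcomes by group until database lock;
- the DMC, stated to be independent of trial conduct, alone reviews unblinded safety data and makes recommendations to the TSC.

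The independence statement is needed because moving access to a DMC whose independence is not stated would not solve the problem. With this wording, 24 evaluable per group and the final 0.05 stay valid.

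If the sponsor keeps one efficacy look, prespecify it at 50% information with a Lan-DeMets O'Brien-Fleming-type spending boundary (interim P about 0.003, final P about 0.049), reviewed by the DMC only. The maximum sample size then rises by a factor of about 1.003: 24 × 1.003 = 24.1 evaluable per group, which is 25 if rounded up strictly.

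The cost is protocol wording. Both committees are already planned. The sponsor gives up ad hoc early stopping for efficacy.

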#### Composition of the data monitoring committee, its role and reporting structure

Neurologists, methodologists, and statisticians will supplement the data monitoring committee (DMC). The DMC will be responsible for overseeing data quality management and safety monitoring. DMC meetings will be held regularly. Clinical Trial Data Management issued by the Chinese National Medical Products Administration.

#### Adverse event reporting and harms

Participants experiencing adverse events (AEs) will be provided with appropriate medical care. If necessary, the intervention will be paused or discontinued based on the clinical judgment of the research team and in consultation with the DMC. A specific protocol will be in place for managing skin irritation or discomfort associated with the tDCS, including immediate cessation of stimulation and application of soothing treatments.

All AEs will be documented in the participant’s case report form (CRF) and followed until resolution or stabilization. Follow-up assessments will be conducted to monitor the participant’s recovery or the persistence of symptoms.

#### Frequency and plans for auditing trial conduct

A dedicated, qualified individual will conduct and monitor this trial. The steering committee will meet regularly to review and evaluate updates.

#### Plans for communicating important protocol amendments to relevant parties (e.g., trial participants, ethical committees)

If the protocol changes during the implementation of the study, a revised protocol will be submitted for approval to the IRB of Yueyang Hospital of Integrated Traditional Chinese and Western Medicine, Shanghai University of TCM.

#### Dissemination plans

We will disseminate the study’s results through conference presentations and publications.

## Discussion

The DLPFC is pivotal in multiple cognitive processes, such as working memory, planning, inhibition, and abstract reasoning. Previous studies indicate that stimulation over the DLPFC can effectively improve cognitive deficits in stroke patients (Shaker et al., 2018; Cha et al., 2022). The AG also plays a vital role in various cognitive functions, including attention, spatial cognition, mental arithmetic, visuospatial processing, inhibitory control, theory of mind, and the processing of semantic information (Bonner et al., 2013; Grob et al., 2024; Park et al., 2024). Stimulation of the AG could enhance autobiographical memory integration (Bonner et al., 2013) and improve associative memory performance (Wang et al., 2014).

Building on these findings, this study hypothesizes that dual-target a-tDCS, focusing on both the DLPFC and AG, will be more effective in improving cognitive function in patients with PSCI compared to single-target a-tDCS on DLPFC. We anticipate significant enhancements in overall cognitive performance, specifically in domains like memory and executive function. Furthermore, we expect that fNIRS measurements will reveal increased activation in the DLPFC and AG and enhanced functional connectivity between cognitive brain networks.

If these hypotheses are confirmed, dual-target a-tDCS could become an effective intervention to improve cognitive outcomes in PSCI patients, potentially exceeding the benefits of conventional single-target interventions. This approach may be integrated into existing rehabilitation programs, thereby contributing to better recovery and an improved quality of life for stroke survivors.

However, the study has several limitations. The sample size is relatively small, and it is a single-center study, which may affect the generalizability of the results. The lack of long-term follow-up means that we could not assess the long-term effects of the intervention. Future research should aim to overcome these limitations by conducting multi-center trials with larger cohorts and longer follow-up periods.

Further exploration is necessary to assess its efficacy across different types and severities of PSCI.

The absence of a dual sham stimulation group may limit the interpretation of tDCS-specific effects versus non-specific intervention effects. Future studies may consider including a dual sham group to further strengthen causal inferences.

Inclusion of both subacute and chronic stroke patients may increase heterogeneity in treatment response. However, this reflects real-world practice, and the planned analyses will explore potential moderating effects of disease phase.

Although some studies suggest combine tDCS and cognitive training may enhance effects, we delivered tDCS alone to isolate its specific contribution and reduce procedural variability in a clinical rehabilitation context.

Additionally, further studies should employ more brain imaging techniques, including MRI and EEG, to comprehensively study the underlying neural mechanisms and better understand how dual-target a-tDCS affects brain connectivity and function.

This study introduces a novel dual-target a-tDCS protocol targeting both the DLPFC and AG to treat PSCI. It aims to fills a gap in the current literature and provides preliminary evidence for a potentially more effective intervention strategy for cognitive rehabilitation in stroke patients.

## Data Availability

Publicly available datasets were analyzed in this study. This data can be found here: not applicable.
